### 1.5. Trial Design

The trial will be conducted according to Consolidated Standards of Reporting Trials (CONSORT) guidelines, and the protocol is drafted in accordance with Standard Protocol Items: Recommendations for Interventional Trials (SPIRIT) guidelines.

The study is designed as a two-arm, exploratory, single-blinded RCT. Participants will be randomize into two groups receiving yoga and light exercise focusing on conventional stretching and mobility. Assessment will be performed at baseline (0 week), after the intervention (after 12+1 week) and at follow-up (after 36+1 week; Figure 1 and Table 1).

## 2. Methods

### 2.1. Study Setting

The intervention will be conducted at the designated facility of R.D. Gardi Medical College, Ujjain, Madhya Pradesh, India. Assessments of primary and secondary outcomes will be conducted at R.D. Gardi Medical College and its associated hospitals.

### 2.2. Inclusion Criteria

Elderly aged between 60 and 80 years who will be willing to participate and who resided in a locality within 2 km from the designated intervention facility will be included. This may also include elderly living in home with family or independently.

### 2.3. Exclusion Criteria

Individuals currently enrolled in any other research study;Individuals advised by doctors to not perform exercises;Individuals involved in current or recent (last two months) practice of yoga or those with regular (three times per week or more) participation in other planned exercises, such as aerobics or strength training;Individuals with health or mobility problems that would interfere with yoga training such as paralysis or inability to sit, stand, walk and severe pain;Individuals having evidence of liver or kidney dysfunction, significant lung diseases, symptoms or signs of congestive heart failure, ischemic heart disease or significant valvar disease and significant visual impairment;Individuals having a resting heart rate >100 beats/min, uncontrolled diabetes mellitus with blood glucose measuring greater than or equal to 400 mg/dL and blood pressure >160 mmHg systolic, >100 mm Hg diastolic;Individuals having major surgery in the last year or planning to undergo future surgeries.

### 2.4. Interventions

#### 2.4.1. Yoga

Elderly who will be randomized to the yoga group will perform the yoga-based intervention three times per week during 12 weeks at a designated facility. The participants will also be encouraged to complete at least one additional yoga session of the same duration at home per week. Yoga will be conducted for 60 min as a classroom session and will accommodate approximately 15–20 participants. Two qualified yoga instructors (male and female) will teach in these classes. The classes will be design to be safe and suitable for elderly and will focused on improving flexibility, balance and strength. Both males and females will be in the same class. The duration of the intervention will be similar to other yoga-based programs reported in literature suitable for elderly [22,47].

The yoga intervention will be standard throughout the study to avoid the risk of intervention variability. Our proposed yoga intervention is based on Hatha Yoga that included physical postures (asanas), breathing exercises and moderate meditation [48]. The following yoga poses will be performed in this order each time: Crocodile pose (Makrasana), Palm tree pose (Tadasana), Hands to feet pose (Hastpadasana), Chair pose (Utkatasana), Twisted pose (Vakrasana), Angle pose (Konasana), Lotus Pose (Padmasana), Yogmudra, Seated Forward Bend Pose (Paschimotanasana), Cobra Pose (Bhujangasana), Locust Pose (Shalabhasana), Wind Relieving Pose (Pawanmuktasana), Stick Pose (Yastikasana), Corpse Pose (Shavasana), Crossed Legs Pose (Sukhasana) and OM Chanting. The description of these poses are described in detail elsewhere [48].

A thirty minute session will be organized by yoga instructors after each session during the first week of the class to give detail instructions regarding the home session. Thereafter every class the yoga instructors will remind participants about the home session. Additionally, a booklet will be given to all participants of yoga group where all instructions, precautions and description of poses and asanas will be described with pictures.

#### 2.4.2. Light Exercise Focusing on Conventional Stretching

In this study we will have active light exercise comparison group to increase the internal validity and adherence. Our comparison group will consist of light exercise focusing on conventional stretching designed to improve mobility. This comparison group will be a genuine light exercise training condition with no strength-training, yoga, meditation or breathing exercises included. The rationale for including such a comparison group, where participants underwent an exercise program at the same duration, frequency and location as the yoga intervention group, is to reduce the likelihood of the Hawthorne effect. This would also make participants happy—but nothing that would give the benefits of real yoga. The light exercise program will include standing positions exercises such as movements of fingers, wrist, elbows, shoulders and legs. The sitting position exercise will include joints movements of the toe, ankle and knee. Lie down exercises will include leg rotation, knee bending and cycling. The comparison group participants will copy the instructor’s movements to ensure that they are not exhausting and strenuous. Engagement of comparison group participants will be done at a similar location and will have the same frequency and duration of training as the yoga group (i.e., 60 min of session thrice a week during 12 weeks at the designated facility and at least one additional session of the same duration at home per week). The sessions will be conducted as a class room session at the same location as the yoga intervention under the supervision of trained instructors (male and female). Each classroom will accommodate approximately 15–20 participants. Both males and females will be in the same class.

A thirty minute session will be organized by trained exercise instructors after each session during the first week of the class to give detail instructions regarding the home session. Thereafter every class the instructors will remind participants for home session. Additionally, a booklet will be given to all participants of the comparison group where all instructions, precautions and descriptions of exercises will be described with pictures.

### 2.5. Follow-Up Visits

All the participants will be weekly followed up from the first week to the 36th week. Participants who will miss any session will be telephonically contacted on the same day by research assistants to enquire about the reason for nonattendance. Participants who will not attend a session due to health reasons will be visited by a research assistant on the same day to document the events. Additionally, all participants will be visited physically by research assistants at home once a week to document adherence (home exercise/yoga), any self-modification in intervention, health-seeking behavior and to record any adverse events in a pre-designed follow-up form (Figure 2).

### 2.6. Strategies to Maintain Adherence

The literature has shown that adherence to physical activity training is low, and this trend is more common in the elderly age group [49]. To minimize participant dropout, one thirty minute face to face session will be organized before the start of the project, in which the project team will communicate with prospective study volunteers. The project team will inform all the components of the study and will address all queries and concerns of participants. All sessions will be conducted by qualified instructors (male and female) of age more than 45 years so that participants would feel less hesitant in following the classes. The yoga and aerobic exercise classes will be especially designed for elderly people. Participants will be provided access to free emergency medical care at all times. All assessments and samplings will be done free of charge at all the three assessment points. The study participants will be recruited within 2 km radius of the facility to minimize the travel time. A pickup and drop facility will also be arranged by the project team if demanded specifically. Daily attendance of participation will be maintained. Weekly follow-up visits will be conducted by research assistants to participants’ homes to document about home session adherence, any changes/modification in yoga exercise intervention at home and documentation of adverse events. Both the classes will be conducted free of charges.

### 2.7. Outcomes Variables

#### 2.7.1. Primary

Well-being will be measured subjectively using the 13 items life satisfaction index, version Z (LSI-Z) [50,51]. Five core components of life satisfaction are measured in the life satisfaction index, namely zest, resolution and fortitude, congruence between desired and achieved goals, positive self-concept and mood tone [52]. Subjective well-being will also be assessed by using a five-item satisfaction with life scale (SWLS) that measures global judgments of one’s life satisfaction [53]. On this scale, the participants show how much they agreed with or disagreed with each item on a scale of 7.

#### 2.7.2. Secondary 

Physical activity and sedentary behavior will be assessed using the short form of the International Physical Activity Questionnaire (IPAQ) [54,55] and the five-item Simple Physical Activity Questionnaire (SIMPAQ) [56].The Berg balance scale, a 14-item objective measure that assesses static balance and fall risks in adults [57,58,59] and modified falls efficacy scale (MFES) [60,61], a 14-item activity questionnaire, which assesses the fear of falling among older adults in various indoor and outdoor activity, will be used to measure mobility and falls.Self-reported depression will be measured using the geriatric depression scale (GDS), which is a 30-item screening instrument for older adults [62,63].Self-reported anxiety will be assessed using the geriatric anxiety inventory (GAI) scale.Mood states and psychological distress will be assessed using the profile of mood state questionnaire (POMS) [64].The perceived stress scale (PSS) will be used to assess pass month subjective stress [65].The brief pain inventory (BPI) short form will be used to measure pain and its severity [66,67].Self-reported sleep quality will be measured using the insomnia severity index (ISI), which is a seven-item self-rated questionnaire [68,69].Cognition will be measured using the mini-mental state examination (MMSE), which is an 11-item questionnaire that tests five areas of cognitive function [70,71].Body mass index (BMI), resting heart rate, blood pressure, waist–hip ratio (WHR), blood glucose, blood lipids and cortisol will be collected to assess cardio metabolic risk factors. Interleukin-6, and tumor necrosis factor-alpha will also be also examined.

#### 2.7.3. Sample Size

The calculation of sample size for this study is based on the effect size reported in a six month long RCT where results of Iyenger yoga on elderly was compared with walking [42]. Based on this study we anticipate that the mean difference (effect size) of around 0.2 on our primary outcome that is well-being in yoga intervention group compared to exercise group. With 80% power, two-tailed significance for the primary between-group comparisons and 1:1 allocation, a total sample of 120 participants is estimated. Assuming a 6-month dropout rate of 20% [72], the total number of participants required at baseline will be 144.

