#### 2.7.4. Recruitment

Recruitment of participants will be conducted using multiple methods of placing advertisements in local newspapers, contacting local pensioner clubs and old age groups and conducting door-to-door surveys in the two-kilometer vicinity of the designated intervention facility. Prospective participants will be provided detailed information of the study. Interested participants will be requested to visit the designated facility at the designated time for eligibility screening. Additional detailed information on the study will be provided verbally and in writing in the local language to all prospective participants prior to eligibility screening. During the course of study we aim to screen at least 600 individuals for eligibility. We anticipated that every fourth volunteer initially selected will be interested and eligible to participate in the study. At each phase we will enroll 15–20 participants, resulting in a total of 144 participants. Staggering the recruitment in this way will make the process more manageable and logistically feasible. The recruitment drive will be done at least 6–8 times until the required number is achieved. New participants will be added to the existing group as per the availability in the class and space vacated by previously admitted participants. Eligibility screening will be performed in week −1 at the designated medical facility of R.D. Gardi Medical College, Ujjain by a team comprising of physician, physiotherapist, psychologist and supported by research assistants trained in social work and public health. The composition of the team that would measure the study outcomes will be consistent throughout the project.

Consent to participate: All the participants will be individually introduced to the study in a face-to-face session with project coordinator and instructors. Participants will be provided with verbal and written information about the purpose of the study, confidentiality and rights to withdraw at any time. Written informed consent will be sought from all the study participants. All data will be analyzed and reported at the aggregate level only; no individual patient data will be released.

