### 2.8. Data Collection

#### 2.8.1. Time Points

Primary and secondary outcomes will be measured at baseline (0 week), post-intervention (12+1 week) and at end point (36+1 week). The assessments will include basic demographic-socio-economic information, anthropometrics measurements, primary and secondary outcome measurements and biological sampling (see Figure 1 and Table 1).

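### Section 2.7.3 inflates 120 for 20% dropout as 120 × 1.2 = 144; the stated assumption needs 120/0.80 = 150, and 144 leaves about 115 completers

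*Protocol article*

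**What the plan says.** Section 2.7.3 (Sample Size) links three figures. For 80% power with a two-tailed test and 1:1 allocation, "a total sample of 120 participants is estimated". Loss to follow-up is then allowed for: "Assuming a 6-month dropout rate of 20% [72], the total number of participants required at baseline will be 144". The abstract and section 2.7.4 (Recruitment) repeat 144 as the number to be enrolled.

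Two other places bear on the point. Section 2.7.4 gives the expected screening yield: "During the course of study we aim to screen at least 600 individuals for eligibility", and "We anticipated that every fourth volunteer initially selected will be interested and eligible to participate in the study". Section 2.8.1 (Time Points) has outcomes "measured at baseline (0 week), post-intervention (12+1 week) and at end point (36+1 week".

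**The concern.** The three figures in section 2.7.3 do not agree. A dropout rate is a fraction of those who start, so the number to enrol comes from dividing the number who must remain by the retained fraction. The plan appears to have added 20% of the final number to itself, which gives a smaller figure. If so, the trial misses its own target of 120 under its own dropout assumption, and a reader who takes 144 as covering 20% loss is misled about the margin.

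The rate is also described as a 6-month rate, while the last visit is at 36+1 weeks. The text does not say which visit the rate is meant to cover.

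**Working it through.** **Inputs**
- Number required before dropout: 120 (section 2.7.3).
- Dropout rate: 20% (section 2.7.3).
- Stated number at baseline: 144 (section 2.7.3, abstract, section 2.7.4).
- Power 80%, two-tailed, 1:1 (section 2.7.3). No alpha is given; two-sided 0.05 is assumed, and only in step 4.
- Screening: at least 600 screened, one in four expected to be interested and eligible (section 2.7.4).

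**Step 1. Reproduce the plan's figure.** n × (1 + d) = 120 × 1.20 = 144. This matches exactly.

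**Step 2. Apply the stated assumption.** n / (1 − d) = 120 / 0.80 = 150, or 75 per arm. The gap is 150 − 144 = 6 participants.

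**Step 3. See what 144 delivers.**
- Completers at 20% loss: 144 × 0.80 = 115.2, about 115, which is 5 short of 120.
- Largest dropout at which 144 still leaves 120: 1 − 120/144 = 16.7%.

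**Step 4. Size the effect on power.** Take 120 (60 per arm) as the size that gives exactly 80% power.
- Standardised difference this implies (normal approximation): (1.960 + 0.842) × √(2/60) = 0.511.
- Power for that difference with 144 × 0.80 / 2 = 57.6 per arm: Φ(0.511 × √(57.6/2) − 1.960), about 78.4%. With 57.5 per arm it is about 78.3%.
- Loss: about 1.6 percentage points.

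**Step 5. Check that 150 is feasible.** 600 / 4 = 150, so the corrected number equals the plan's own expected yield, with no margin beyond it.

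**The case against.** **The slip is small.** It amounts to six participants and under two points of power. Section 3 plans an intention-to-treat mixed linear model, which can use participants with partial follow-up, so completers are not the whole analysis set. Section 1.5 calls the trial exploratory. All of this stands and limits the importance of the point. It does not make the sentence correct: the text says how many are required at baseline under a stated dropout rate, and that number is wrong. No other section corrects it.

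**A larger shortfall at 36 weeks.** A reader might infer that a 6-month rate understates loss at the last visit and that the trial therefore falls well short there. Extending 20% over 26 weeks at a constant hazard leaves 144 × 0.80^(36/26), about 106, at week 36. The document does not support this as a finding, for three reasons.
- No section says which visit carries the primary comparison. In section 2.8.1 the phrase "post-intervention (12+1 week) and at end point (36+1 week" labels the last visit and does not name the primary analysis time.
- Under the same constant-hazard assumption, 144 × 0.80^(13/26), about 129, remain at 12+1 weeks, which is above 120.
- Weeks 12 to 36 span 24 weeks, so the 6 months could mean the period after the intervention.

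**The stated power fails because of this step.** A reader might infer this too. The dropout step alone costs about 1.6 points. Whether 120 follows from an effect size of around 0.2 is a separate and larger question. Read as a standardised difference, 0.2 would need about 786 in total (two-sided alpha 0.05 assumed). Correcting the inflation does not settle that question.

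**Conclusion.** The stated baseline requirement is wrong as written. Under the plan's own 120 and 20%, the figure is 150, and this part rests on no outside assumption. The practical impact is minor: power falls from 80% to about 78%, taking 120 as correct and assuming two-sided alpha 0.05.

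The mismatch between a 6-month rate and a last visit at 36+1 weeks is a secondary matter of clarity. The document does not establish a shortfall at week 36.

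**What to change.** Correct the dropout sentence in section 2.7.3 in one of two ways.
- **Keep 144**, and state either that it yields about 115 completers at 20% dropout or that it allows for 16.7% dropout. This costs one sentence; the 144 in the abstract and section 2.7.4 can stay.
- **State 150** as the number required at baseline, and carry it into the abstract and section 2.7.4. This costs six more participants, within the yield expected from screening 600.

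In the same sentence, say which visit the 20% applies to. Do not write in a completer figure for week 36: it would rest on a constant-hazard assumption and on a primary time point that the text does not state.

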#### 2.7.4. Recruitment

Recruitment of participants will be conducted using multiple methods of placing advertisements in local newspapers, contacting local pensioner clubs and old age groups and conducting door-to-door surveys in the two-kilometer vicinity of the designated intervention facility. Prospective participants will be provided detailed information of the study. Interested participants will be requested to visit the designated facility at the designated time for eligibility screening. Additional detailed information on the study will be provided verbally and in writing in the local language to all prospective participants prior to eligibility screening. During the course of study we aim to screen at least 600 individuals for eligibility. We anticipated that every fourth volunteer initially selected will be interested and eligible to participate in the study. At each phase we will enroll 15–20 participants, resulting in a total of 144 participants. Staggering the recruitment in this way will make the process more manageable and logistically feasible. The recruitment drive will be done at least 6–8 times until the required number is achieved. New participants will be added to the existing group as per the availability in the class and space vacated by previously admitted participants. Eligibility screening will be performed in week −1 at the designated medical facility of R.D. Gardi Medical College, Ujjain by a team comprising of physician, physiotherapist, psychologist and supported by research assistants trained in social work and public health. The composition of the team that would measure the study outcomes will be consistent throughout the project.

Consent to participate: All the participants will be individually introduced to the study in a face-to-face session with project coordinator and instructors. Participants will be provided with verbal and written information about the purpose of the study, confidentiality and rights to withdraw at any time. Written informed consent will be sought from all the study participants. All data will be analyzed and reported at the aggregate level only; no individual patient data will be released.

#### 2.7.5. Randomization and Blinding

The randomization sequence by gender will be generated by an external statistician who is not directly involved in the implementation of the intervention. Each allocation sequence will be transferred into separate sealed envelopes by an assistant nominated by the statistician, which will not be part of the study. Immediately after baseline assessments, the allocation sequence in a sealed envelope will be opened by the principal investigator or project coordinator together with eligible participants. Participants will be informed whether they are allocated to the yoga or light exercise group. At baseline, participants will be requested to not discuss their treatment allocation with the research team responsible for conducting follow-up assessments where a different set of research team blinded to the participant’s allotted group will conduct these assessments. The allotted group will be kept confidential and will be un-blinded only if participants withdraws or due to adverse events. The instructors will also be informed about the allotted group for proper management of yoga/exercise classes.

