### 3.1. Assessment of Adverse Events

In the proposed study, the potential risks of adverse events are minimal. Most frequently anticipated adverse events are muscle strains, soreness, knee pain, Achilles tendon, back spasms, neck pain, vertigo, migraine and reoccurrence of prior lower back pain or shoulder problems [73].All sessions will be conducted by qualified yoga instructors at a health center or near a health center in Ujjain. Participants will be provided access to emergency medical care at all times. The interventions will be specially designed for elderly. A team of physicians will screen all potential participants and will exclude those with health problems that may hinder participation..All adverse events will be recorded, and followed up by research assistants. Adverse events will be formally assessed during the weekly home visits of study participants where participants will be asked to inform project team of any health related events they encountered in past week. Adverse events will also be communicated to the team of physicians for assessments and medical management.

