The present understanding came from mainly studies conducted in residential care homes [80]. Most of other studies did not included elderly. There is a requirement of well-designed community-based follow studies to assess long term changes and outcomes. We feel that with yoga being a practical, easy and feasible exercise that it can help in emotional and physical betterment and ultimately wellbeing in an elderly group. This project aimed to encourage participants to initiate and continue a yoga-based activity after study completion. We anticipate significant improvements in several health domains. The intervention would benefit participants, their families and society in terms of (anticipated) lower health costs. Moreover, the study results may be of broader use in other settings. We would use the standardized measurements and blinded follow-up assessments, to reduce the assessment bias.

However, there may be some possible limitations in this study. This study concerns with the overestimation of intensity/duration of physical activity assessed through subjective measurement, due to social desirability of responses i.e., there is a possibility that contact with other participants/trainers/research assistants may increase wellbeing in studied population. Generalizability of study will be limited to similar settings and conditions. We will recruit only those individuals that will show interest towards devoting time in physical activities.

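### The unblinding rule permits follow-up assessors to learn the arm after withdrawal or an adverse event, with no need condition and no named recipient

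*Protocol article*

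**What the plan says.** Section 1.5 gives the design: "The study is designed as a two-arm, exploratory, single-blinded RCT". Section 2.7.5 then sets out who knows what. On opening the envelope: "the allocation sequence in a sealed envelope will be opened by the principal investigator or project coordinator together with eligible participants". On participants: "Participants will be informed whether they are allocated to the yoga or light exercise group". Instructors are also told, so that they can run the classes. For follow-up, "a different set of research team blinded to the participant’s allotted group will conduct these assessments". The rule at issue comes next: "The allotted group will be kept confidential and will be un-blinded only if participants withdraws or due to adverse events".

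Three other places bear on it.

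- Section 3.1 on ascertainment: "Adverse events will be formally assessed during the weekly home visits of study participants". Section 2.5 and Table 1 carry those visits to week 36.
- Section 3.1 on the kind of event: "Most frequently anticipated adverse events are muscle strains, soreness, knee pain", followed by further, mostly musculoskeletal, complaints. No arm is named, and the overall risk is called minimal.
- Section 4 on what the blinding is for: "We would use the standardized measurements and blinded follow-up assessments, to reduce the assessment bias".

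**The concern.** An unblinding provision normally exists because the people caring for a participant do not know the treatment and may need to. That reason is largely absent here: the participant knows which class they attend, and so do the instructors and whoever opened the envelope. The party with blinding to lose is the assessment team, and the article shows no reason why that team would need the allocation.

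Withdrawal and adverse events both occur after randomisation and may be related to arm and to outcome. Blinding lost under this rule would be lost in a selected group, not at random. Where the assessor runs or scores the test, knowing the arm can shift the score, and the article relies on blinded follow-up to limit that bias.

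**Working it through.** The article states no figure on this point, so there is none to reproduce. The check sets the statements side by side, then gives the one count the article supports and an illustration under labelled assumptions.

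**Step 1. Who could be unblinded?**

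| Party | Knowledge of arm | Source |
|---|---|---|
| Participant | Told | 2.7.5 |
| Investigator or coordinator | Opens the envelope | 2.7.5 |
| Instructors | Told | 2.7.5 |
| Follow-up assessors | Blinded | 2.7.5 |
| Physicians managing adverse events | Not stated | 3.1 |
| Community advisory board | Not stated; told of adverse events | 2.11 |

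The assessors are the only group stated to be blinded. The rule does not exclude them as recipients.

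**Step 2. What limits the rule?** It has two conditions, withdrawal and adverse events. It sets no severity threshold, no test of medical need and no recipient. Its wording restricts unblinding to these cases but does not say that unblinding follows in each one.

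**Step 3. Size of the withdrawal condition.** Inputs are 144 randomised and 20% dropout by 6 months (section 2.7.3).

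144 × 0.20 = 28.8, about 29 participants.

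This counts people to whom the rule could apply. It is not a count of biased assessments: some who leave will have no later assessment.

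**Step 4. Size of the adverse-event condition.** The article gives no rate, overall or by arm, so this cannot be computed.

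**Step 5. Could it matter for an assessor-scored outcome?** This is an illustration only. Let u be the share of assessments made unblinded in each arm, and b the shift in score, in SD, that an unblinded assessor introduces. Neither is in the article.

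- Yoga scored up and control scored down: bias = b × (u_yoga + u_control).
- Same direction of shift in both arms: bias = b × (u_yoga − u_control).

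With b from 0.1 to 0.3 SD:

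| u_yoga | u_control | Opposite directions | Same direction |
|---|---|---|---|
| 0.20 | 0.20 | 0.1 × 0.4 to 0.3 × 0.4 = 0.04 to 0.12 | 0 |
| 0.30 | 0.10 | 0.1 × 0.4 to 0.3 × 0.4 = 0.04 to 0.12 | 0.1 × 0.2 to 0.3 × 0.2 = 0.02 to 0.06 |

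For scale only, section 2.7.3 plans on a difference of around 0.2 on the primary outcome. The first row shows that bias does not require more unblinding in one arm. It also shows that the bias vanishes if assessors shift both arms alike.

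**Step 6. Which outcomes?** The primary outcome is well-being on the LSI-Z and SWLS, which section 1.4 treats as self-reported. Participants know their arm, so assessor blinding gives these scales little protection to lose. Laboratory measures are hardly exposed. That leaves the Berg balance scale, the MMSE and any questionnaire given by an interviewer.

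**The case against.** The strongest reply is that the sentence restricts disclosure, and that its natural recipient is the physician team. Section 3.1 sends adverse events to physicians for assessment and management, and no section says those physicians know the arm. On that reading the assessors stay blinded and the sentence needs no change. This is a fair possibility, and it is why the point is about what the rule permits and not about what will happen. It does not settle the matter, because the sentence names no recipient. Nor does the article establish that physicians and outcome assessors are separate people: section 2.7.4 puts a physician on the screening team and does not list who assesses outcomes at follow-up.

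A second reply is that an article condenses the full protocol, and that recipient and logging are details left to it. That would answer a complaint about silence. Here the article states a rule, and the rule as stated is too open.

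A reader might infer three stronger things, none of which the article supports.

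- That every adverse event, down to a sore muscle, unblinds the assessor. The wording limits when unblinding may occur; it does not require it.
- That the yoga arm would be unblinded more often. The comparison programme is described as light, so more events under yoga is conceivable. But section 2.4.2 gives both arms the same frequency and duration, the event list in section 3.1 names no arm, and nothing indicates the direction of withdrawals. Any assumed weekly event rate would come from outside the article.
- That the primary result is compromised. Step 6 shows why it is little affected. Blinded assessment is also not the only safeguard named in section 4, which lists standardised measurement beside it.

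**Conclusion.** The concern holds in a limited form. The rule permits the only stated blinding in the trial to be lifted for a non-random subset, without a need condition or a named recipient, and so weakens a safeguard on which the Discussion relies. The supported size is about 29 of 144 participants to whom the withdrawal condition could apply, taking the planned 20% dropout at face value. The frequency of unblinding through adverse events, and any difference between arms, cannot be stated. The bias range of 0 to 0.12 SD in the illustration rests entirely on assumed unblinding shares and assessor shifts. The consequence falls on assessor-dependent secondary outcomes. The conclusion assumes that assessors are among the possible recipients, which the text allows but does not assert.

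**What to change.** Reword the sentence in section 2.7.5 along these lines: follow-up outcome assessors remain blinded for every participant, including those who withdraw from classes or have an adverse event; where physicians need the allocation, they obtain it from those who already hold it, and it is not passed to the outcome assessors; any assessor unblinding, whether accidental or deliberate, is logged with its date and reason and reported by arm.

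Medical management is unchanged, since the information still reaches the physicians. The cost is the log and the discipline of keeping adverse-event handling separate from outcome assessment. If any physician also assesses outcomes, that assessment would need to go to someone else for the participants concerned.
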